### Sample size calculation

The sample size was calculated based on a previous meta-analysis^14^ that found NOL-guided analgesia protocols to decrease intraoperative remifentanil consumption (standardised mean difference [SMD] –0.68; 95% confidence interval: –1.13 to 0.24; *P*=0.003). We will focus on one disease and procedure and the NOL index alone in the present trial, and thus, we expect less variability. Accordingly, we estimated SMD as 0.8 to obtain group sample sizes of 25 patients achieving 80% power with a significance level of 0.05. Considering a dropout rate of 10%, we will enrol 27 patients in each group.

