#### Allocation

Participants will be randomly assigned to each group with a 1:1 allocation using a web-based service (QuickCalcs; GraphPad Software, La Jolla, CA, USA). The block sizes will not be disclosed to ensure concealment. Randomisation will not be stratified, as there is little possibility of imbalance between each group because we selected only one procedure.

Blinding is only possible for the participants. The anaesthesiologists will open a sealed envelope containing the group name before the operation. The allocation manager will perform randomisation. Participants will be unblinded after 3 months of follow-up, if requested.

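### Enrolling 27 per arm does not keep the planned 25 after the stated 10% dropout: power is about 77% at SMD 0.8 with 24 evaluable per arm, and the cited confidence interval contradicts its own P value

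*Protocol article*

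**What the plan says.** All the planning figures stand in the protocol article under Sample size calculation. The starting point is a meta-analysis of NOL-guided analgesia and remifentanil consumption, reported as "SMD] –0.68; 95% confidence interval: –1.13 to 0.24" with P=0.003. The plan then moves to a larger effect, reasoning: "We will focus on one disease and procedure and the NOL index alone in the present trial, and thus, we expect less variability". From this it concludes: "we estimated SMD as 0.8 to obtain group sample sizes of 25 patients achieving 80% power with a significance level of 0.05". The allowance for losses follows: "Considering a dropout rate of 10%, we will enrol 27 patients in each group". This gives the 54 patients named in the abstract.

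The Allocation section fixes a 1:1 ratio, and Statistical methods names an unpaired t-test for the primary outcome, the mean intraoperative remifentanil infusion rate. The article does not say whether the 0.05 level is one- or two-sided.

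**The concern.** Three things in one short paragraph do not sit well together.

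- **Dropout step.** An allowance for dropout should bring the expected number of evaluable patients back to the number that the power calculation needs. Here 27 per arm with 10% loss leaves fewer than 25, so the 80% is attached to a number that the plan does not expect to analyse.
- **Planning effect.** It is larger than the effect in the only evidence cited, and the reader is not told what power remains at the cited value.
- **Cited interval.** It includes zero, yet stands beside P=0.003.

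What is at stake is how the trial will be read. Anyone judging a non-significant primary result will take 80% as the trial's power. The plan's own enrolment and dropout figures support a slightly lower value at SMD 0.8, and a clearly lower one if the meta-analytic estimate is nearer the truth.

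**Working it through.** **Inputs.** From Sample size calculation: SMD 0.8 (planning), SMD –0.68 (cited), alpha 0.05, power 80%, dropout 10%, 27 enrolled per arm. From Allocation: ratio 1:1. From Statistical methods: unpaired t-test. Assumption: two-sided alpha. A one-sided 0.05 test would need only 21 per arm, so the stated 25 implies two-sided.

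**1. Reproducing the plan's figure.** By the normal approximation:

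n per arm = 2 × (1.960 + 0.842)² / 0.8² = 24.5, rounded up to 25.

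Power at 25 is 80.7%. The stated 25 therefore reproduces. For the planned t-test (noncentral t distribution) the exact requirement is 25.5, so 26 per arm, and power at 25 is 79.2%. The gap between the two formulas is small.

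**2. The dropout step.**

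- Dividing by the retained fraction: 25/0.9 = 27.8, rounded up to 28.
- Simply adding 10%: 25 × 1.1 = 27.5, also rounded up to 28.
- What the plan's 27 leaves: 27 × 0.9 = 24.3.

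By either convention the enrolment is one patient per arm short.

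**3. Power at the numbers the plan leads to** (two-sided 0.05):

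| Evaluable per arm | SMD 0.8, t-test | SMD 0.8, normal approx. | SMD 0.68, t-test |
|---|---|---|---|
| 24 (after 10% loss) | 77.4% | 79.1% | 63.5% |
| 25 (stated) | 79.2% | 80.7% | 65.4% |
| 26 | 80.8% | 82.2% | 67.2% |
| 27 (no loss) | 82.2% | 83.6% | 68.9% |

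With 24 per arm the t-test reaches 80% power at an SMD of 0.83; with 25 per arm, at 0.81.

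**4. What the step from 0.68 to 0.8 requires.** At an unchanged mean difference, the SD must shrink by the factor 0.68/0.8 = 0.85, that is, by 15%. The article gives no figure for this. If the SMD were 0.68, the t-test would need 35 evaluable per arm for 80% power.

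**5. The cited interval.** For a 95% interval, SE = (upper – lower)/3.92.

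- As printed (upper limit +0.24): midpoint (–1.13 + 0.24)/2 = –0.445, not –0.68. SE = 1.37/3.92 = 0.349, z = 0.68/0.349 = 1.95, P about 0.05.
- With upper limit –0.24: midpoint –0.685. SE = 0.89/3.92 = 0.227, z = 0.68/0.227 = 3.0, P about 0.003.

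Only the second version agrees with both the estimate and the P value printed beside it.

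**The case against.** The strongest reply is that the calculation is sound. The stated 80% belongs to 25 analysed patients at SMD 0.8, and it reproduces by a standard formula. This stands: neither the 25 nor the choice of formula is an error. By that same formula even 24 per arm gives 79.1%, so the dropout slip alone costs between one and three points, depending on the formula. This also stands. The slip remains, because the plan's own 10% does not lead back to its own 25.

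A second reply is that 10% may be cautious here. The primary outcome is intraoperative and comes from the medical record, so losses at later follow-up cannot remove it. That is fair. A reader might infer that 77% is the most the trial can reach, and this would be wrong: with no loss the power is 82%, and with one loss per arm it is 80.8%. The 77% is what follows from the plan's own dropout rate.

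A third reply is that 0.68 was openly cited and openly set aside, with a reason. This too stands. A reader might infer from the 64% that the stated power is false; the document does not support that, because 64% is power at an effect that the plan chose not to use. Nor does it follow that 0.8 is unattainable. A more uniform population can lower the within-trial SD. The minimum infusion rate in the NOL group limits the mean difference but may also reduce spread, so its net effect on the SMD is unknown. The absence of an SD from the hospital's own records is detail that an article may leave to the full protocol, and is not held against the plan.

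Finally, the interval is a quoted outside result and does not enter the calculation. That is true, but as printed it contradicts the figures next to it.

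**Conclusion.** The point holds as a correction to stated figures, not as a failure of the design. Enrolment is one patient per arm short of what 25 evaluable patients and 10% dropout require. With 24 evaluable per arm, the planned two-sided t-test has about 77% power at SMD 0.8 rather than 80%. This rests on a two-sided 0.05 level, the plan's own 10% loss falling equally on both arms, and 24.3 taken as 24.

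The larger uncertainty lies in the planning effect. The rise from 0.68 to 0.8 has a qualitative reason and no figure, and power at 0.68 would be about 64% with 24 per arm. That is sensitivity to a declared assumption and should be reported as such.

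The printed confidence interval is internally inconsistent. A lost minus sign on the upper limit is the likely cause, but only the source can confirm it.

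**What to change.** Keep 54 patients and restate the paragraph along these lines: 27 per arm are enrolled; with 10% loss about 24 per arm are evaluable; a two-sided unpaired t-test at 0.05 then has about 77% power at SMD 0.8 (82% with no loss), and the SMD detectable with 80% power is 0.83; as a sensitivity figure, power at the meta-analytic SMD of 0.68 is about 64% with 24 per arm. Check the upper confidence limit of the cited meta-analysis against the source and correct its sign.

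The cost is a change of wording and a less favourable stated power. No patients, visits or analyses are added.

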#### Recruitment

All patients scheduled for RARP will be recruited at Nara Medical University. The investigators will select eligible participants and provide an explanation regarding this study.

#### Allocation

Participants will be randomly assigned to each group with a 1:1 allocation using a web-based service (QuickCalcs; GraphPad Software, La Jolla, CA, USA). The block sizes will not be disclosed to ensure concealment. Randomisation will not be stratified, as there is little possibility of imbalance between each group because we selected only one procedure.

Blinding is only possible for the participants. The anaesthesiologists will open a sealed envelope containing the group name before the operation. The allocation manager will perform randomisation. Participants will be unblinded after 3 months of follow-up, if requested.

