Therefore, we designed a single-centre single-blinded RCT to investigate the impact of a NOL-directed opioid administration protocol on intraoperative remifentanil consumption, measuring inflammatory biomarker levels to investigate unintended stress responses. Eligible patients will be randomly allocated to receive NOL-directed intraoperative opioid management (NOL group) or conventional intraoperative analgesic management (control group), with a 1:1 allocation with block randomisation.

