### Primary and secondary outcomes

The primary outcome is the mean intraoperative remifentanil infusion rate per ideal body weight (IBW). The infusion rate will be calculated as total amount of intraoperative remifentanil divided by the duration of the surgery, and IBW will be calculated as 22 × (height in metres).^2^

Plasma inflammatory biomarker concentrations, including IL-6 and CRP, will be compared between the groups as secondary outcomes. The time points for the assessment of these biomarkers were selected based on previous studies,^6^^,^^8^ which showed that IL-6 concentrations increased 0–2 h postoperatively and peaked at 12–24 h postoperatively, whereas CRP concentrations showed a delayed peak at 1–3 days postoperatively. As in previous studies,^3^^,^^6^ we will measure cortisol concentrations at baseline and at the end of surgery.

Variations in the NOL index at the start of pneumoperitoneum and in response to postural changes will be investigated as secondary outcomes. These sub-analyses will provide information on the clinical limitations of anaesthetic management using the NOL index.

The secondary outcomes include the following: (i) perioperative IL-6, CRP, and cortisol concentrations (IL-6 and cortisol will be assessed by electrochemiluminescence immunoassay); (ii) total remifentanil dose; (iii) variation from baseline in the NOL index 60–90 s after each of tracheal intubation, the onset of pneumoperitoneum, and any postural changes; (iv) postoperative pain score (numeric rating scale [NRS]) 2 h after surgery and on postoperative Days 1, 2, 3, and 7; (v) incidence of postoperative nausea and vomiting (PONV) 2 h after surgery and on postoperative Days 1, 2, and 3; (vi) dose of postoperative opioid fentanyl and analgesic agents; (vii) occurrence of chronic pain at 3 months postoperatively; (viii) dose of vasoactive agents (phenylephrine, ephedrine, norepinephrine, and atropine); (ix) duration of hypotension (MAP below 60 mm Hg), hypertension (systolic BP over 160 mm Hg), bradycardia (heart rate less than 40 beats min^−1^), and tachycardia (heart rate more than 100 beats min^−1^).

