#### Data collection methods

Consumption of opioid and other agents, NOL index, information during surgery, and complications will be collected from electronic medical records and transferred to paper case report forms. Blood tests for IL-6, CRP, and cortisol will be taken at designated points. NRS and PONV will be assessed through face-to-face interviews. Patients will complete three questionnaires (PCS, HADS, and WHODAS 2.0) on the day before the surgery. The HADS, WHODAS 2.0, and NRS questionnaires will be sent to participants by mail 3 months later and sent back to the investigators after completion.

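### The protocol rules out blinding for everyone but the participant, which is broader than its design requires; early pain and PONV collection and the analysis could be protected cheaply

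*Protocol article*

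**What the plan says.** The introduction of the protocol article gives the design label: "we designed a single-centre single-blinded RCT". The Allocation section explains it: "Blinding is only possible for the participants". The same section says who learns the arm before surgery: "The anaesthesiologists will open a sealed envelope containing the group name before the operation". It makes an allocation manager responsible for randomisation and sets the end of the participant's blind: "Participants will be unblinded after 3 months of follow-up, if requested".

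Two secondary outcomes matter here, items (iv) and (v) under Primary and secondary outcomes: "postoperative pain score (numeric rating scale [NRS]) 2 h after surgery and on postoperative Days 1, 2, 3, and 7" and "incidence of postoperative nausea and vomiting (PONV) 2 h after surgery and on postoperative Days 1, 2, and 3". Data collection methods says how they are obtained: "NRS and PONV will be assessed through face-to-face interviews". The later follow-up is different: "The HADS, WHODAS 2.0, and NRS questionnaires will be sent to participants by mail 3 months later".

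**The concern.** The Allocation sentence does not merely leave interviewer and analyst blinding undescribed. It says that no blinding beyond the participant is possible. This is therefore not a gap that a full protocol or an analysis plan could fill without comment: a document that blinded either role would contradict it.

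At stake is the credibility of the early pain and PONV comparisons. Both are subjective. An interviewer who knows the arm can, without meaning to, phrase or follow up a question differently, record a borderline answer differently, or let the allocation slip. The last would weaken the only blind the trial has, which is meant to hold until 3 months. The introduction also cites lower postoperative pain scores under NOL guidance, so the early NRS results will be read with that expectation in mind. The intraoperative titration cannot be hidden from the person doing it, which is a reason to protect the steps that can be.

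**Working it through.** No figure in the plan decides this point, so the check sets the sections side by side.

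1. **Where the arms differ.** The Control group and NOL group sections differ in opioid management during the operation: discretionary dosing with the index concealed, against a fixed scheme with index-driven titration. The last arm-specific step is the fentanyl dose around robot de-docking. Postoperative analgesia is described under Both groups and is common to the two arms.

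2. **Who is shown to need or hold the allocation.** The anaesthesiologists, who must follow one scheme or the other, and the allocation manager. No section gives a reason why a postoperative interviewer or an analyst must know it.

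3. **When the interviews take place.** The earliest is 2 h after surgery and the latest is Day 7, so all follow the end of the allocated treatment.

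4. **How many readings are exposed.**
   - NRS: 2 h, Days 1, 2, 3, 7 = 5
   - PONV: 2 h, Days 1, 2, 3 = 4
   - Total: 5 + 4 = 9 outcome-by-time comparisons, in 2 of the 9 listed secondary outcomes

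5. **What the interviewer cannot reach.**
   - The primary outcome is a recorded dose divided by duration of surgery and ideal body weight.
   - IL-6, CRP and cortisol are laboratory measurements.
   - The 3-month NRS, HADS and WHODAS 2.0 are completed by the patient and returned by post.

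6. **Who supplies the exposed data.** The participant, who is blinded throughout these time points. Bias would have to enter through how the question is put, how the answer is written down, or the arm being disclosed.

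7. **Whether an alternative is within the trial's means.** The 3-month NRS is already self-completed, so collecting a pain score without an interviewer is something the trial already does. Coded arm labels need no change to data collection.

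8. **Effect on the sample size.** None. The 25 per group (27 enrolled) is set for the primary outcome, which this point does not touch.

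Steps 1 to 3 show that the impossibility claim does not follow from the design. Steps 4 to 6 bound the consequence.

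**The case against.** The strongest reply is that the person who rates the pain is blinded. NRS is the patient's own number and PONV is an event the patient reports. Both arms wear the same finger probe, which supports the participant's blind. This stands, and it narrows the concern to prompting, recording and accidental disclosure. A reader might infer that an unblinded observer rates these outcomes; the document does not support that.

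A second tempting inference is that the anaesthesiologist who ran the case later asks that patient for the pain score. No section names the interviewer, and an article commonly leaves such detail to the full protocol. The sentence does not exclude that arrangement, but neither does it describe it, so it should not be alleged.

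Third, the document says nothing specific about the analyst, and coded-label analysis is often placed in the analysis plan. The primary analysis is also fixed as an unpaired t-test, which leaves limited room for discretion. So one cannot say that the analyst will see the arms. What remains is that the sentence, read literally, denies that the analyst could be blinded, which is incorrect. Some choices are also left open under Statistical methods, such as the conditional Kaplan–Meier repeat.

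Fourth, a promise of interviewers unaware of the arm at every time point assumes staffing that the document does not describe. The independent data monitoring staff are there to check accuracy and completeness; using them to collect outcomes would compromise that role. This objection also stands, which is why the patient-marked form comes first in the fix.

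**Conclusion.** The concern holds in limited form. The Allocation sentence is too broad on the protocol's own facts: blinding of early outcome collection and of the analysis is possible, and the text says it is not. The interviewer exposure is 9 readings in two secondary outcomes, through prompting, recording or accidental unblinding. Its size cannot be derived from the document, and it could be nil if the interviewers turn out to be unaware of the arm.

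A reader might go further and conclude that the trial's main result is open to observer bias in outcome assessment. The document does not support that, because the primary outcome is a recorded dose, the biomarkers are assayed, and the 3-month questionnaires involve no interviewer.

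The conclusion assumes that the arms do not differ in planned care after surgery, as the Both groups section indicates, and that the sentence means what it literally says. It is a cheap improvement worth making, not a threat to the primary comparison.

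**What to change.** Replace the sentence in Allocation with text along these lines: *The anaesthesia team cannot be blinded to the allocation. Participants are blinded until the 3-month follow-up is complete. NRS and PONV up to Day 7 are marked by the participant on a form or, where existing staff allow, collected by someone unaware of the allocation who does not consult the anaesthetic record. The analysis is run with arms coded A and B until it is final.* Change the face-to-face interview sentence in Data collection methods to match.

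The cost is a short form to hand out and check for completeness at each time point, and a coding step before analysis. Treatment, assessment times and sample size do not change, and the form needs no additional assessor. If interviews are kept at some time points, the protocol should say who conducts them and whether that person knows the arm.

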#### Data collection methods

Consumption of opioid and other agents, NOL index, information during surgery, and complications will be collected from electronic medical records and transferred to paper case report forms. Blood tests for IL-6, CRP, and cortisol will be taken at designated points. NRS and PONV will be assessed through face-to-face interviews. Patients will complete three questionnaires (PCS, HADS, and WHODAS 2.0) on the day before the surgery. The HADS, WHODAS 2.0, and NRS questionnaires will be sent to participants by mail 3 months later and sent back to the investigators after completion.

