**Fig 3 fig3:**
[figure not shown]
Assessment schedule. BP, blood pressure; CRP, C-reactive protein; HADS, Hospital Anxiety and Depression Scale; HR, heart rate; IL-6, interleukin-6; NOL, nociception level; NRS, numeric rating scale; PCS, Pain Catastrophizing Scale; PONV, postoperative nausea and vomiting; WHODAS 2.0, WHO Disability Assessment Schedule 2.0.

To evaluate chronic post-surgical pain, we will use the Japanese versions of three questionnaires in addition to the NRS: Pain Catastrophizing Scale (PCS),^10^ Hospital Anxiety and Depression Scale (HADS),^11^ and WHO Disability Assessment Schedule 2.0 (WHODAS 2.0).^12^ Patients will complete the three questionnaires on the day before surgery, and the HADS and WHODAS 2.0 at 3 months postoperatively by mail (Fig. 3).

The nociceptive response (NR), a recently proposed new concept that quantifies nociceptive stimuli but has not yet been fully applied clinically, will be measured as an exploratory outcome to examine the relationship between NR and NOL. The NR is calculated as –1+2/(1+exp[–0.01 HR–0.02 SBP+0.17 PI]), where HR is heart rate, SBP is systolic blood pressure and PI is the perfusion index.^13^

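### The text schedules no pain score before surgery, so pain at 3 months that predates the operation cannot be separated from new post-surgical pain (secondary outcome vii)

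*Protocol article*

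**What the plan says.** All references are to the protocol article.

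- **The outcome.** Primary and secondary outcomes lists "vii) occurrence of chronic pain at 3 months postoperatively". The text after the Figure 3 legend gives the purpose and instruments: "To evaluate chronic post-surgical pain, we will use the Japanese versions of three questionnaires in addition to the NRS".
- **Before surgery.** That text continues: "Patients will complete the three questionnaires on the day before surgery, and the HADS and WHODAS 2.0 at 3 months postoperatively by mail". Data collection methods repeats the preoperative list: "Patients will complete three questionnaires (PCS, HADS, and WHODAS 2.0) on the day before the surgery". Neither place names the NRS before surgery.
- **At 3 months.** "The HADS, WHODAS 2.0, and NRS questionnaires will be sent to participants by mail 3 months later".
- **Other NRS times.** Outcome (iv) is "postoperative pain score (numeric rating scale [NRS]) 2 h after surgery and on postoperative Days 1, 2, 3, and 7". All of these are postoperative.
- **Eligibility.** Men aged 20–85 yr, ASA 1–3, may enter. The exclusions cover emergency surgery, beta blockers, oral steroids, lack of a usable finger and inability to consent. Prior pain is not among them.
- **Analysis.** Statistical methods plans group estimates and a between-group difference with 95% confidence intervals for (vii), and mentions no use of preoperative pain.

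**The concern.** Post-surgical pain is a statement about change: the pain must be new, or worse than before. Of the instruments named at 3 months, only the NRS scores pain, and the text gives it no preoperative counterpart. By their names, the three preoperative questionnaires cover catastrophizing, anxiety and depression, and disability. A man with long-standing joint pain and a man with pain that began after the operation could therefore return the same 3-month NRS, and nothing the text schedules before surgery would distinguish them.

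At stake is what outcome (vii) can support. The reported incidence may include pain unrelated to the operation, and any effect of NOL-directed analgesia on new pain would be diluted by cases it could not have prevented. An analysis plan written later cannot repair this, because it cannot use a baseline that was never collected.

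The gap also departs from the trial's own pattern. The NOL index is analysed as variation from baseline, each biomarker has a sample before the operation, and HADS and WHODAS 2.0 are taken both before surgery and at 3 months.

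**Working it through.** **Step 1: the schedule as written.**

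| Measure | Before surgery | 3 months |
|---|---|---|
| PCS | yes | no |
| HADS | yes | yes |
| WHODAS 2.0 | yes | yes |
| NRS (pain) | not listed | yes |

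The two descriptions of the preoperative list agree with each other, and both give a count of three.

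**Step 2: inputs for the size.** The article gives no expected rate for outcome (vii), so there is no stated figure to reproduce. From Sample size calculation: 27 patients enrolled per group. Assumed, not in the article:

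- q, the probability of new chronic pain in those without prior pain: 10%.
- π, the prevalence of prior pain: 10% or 20%, equal in both arms.
- All prior pain persists to 3 months and is scored as pain.

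**Step 3: incidence.** Observed rate = π + (1 − π)q.

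- π = 0.10: 0.10 + 0.90 × 0.10 = 0.19. Share predating surgery: 0.10/0.19 = 53%.
- π = 0.20: 0.20 + 0.80 × 0.10 = 0.28. Share predating surgery: 0.20/0.28 = 71%.

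**Step 4: group difference.** With new-pain rates q₁ and q₂, the observed difference is [π + (1 − π)q₁] − [π + (1 − π)q₂] = (1 − π)(q₁ − q₂). A true difference keeps 90% of its size at π = 0.10 and 80% at π = 0.20, whatever q₁ and q₂ are. For example, with assumed new-pain rates of 30% and 15% (15 points apart):

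- π = 0.10: 37% against 23.5%, a difference of 13.5 points.
- π = 0.20: 44% against 32%, a difference of 12 points.

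**Step 5: noise.** With 27 per group and the same rate p in both arms, the SD of the between-arm difference is √(2p(1 − p)/27), and the 95% half-width is 1.96 times that.

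- No prior pain, p = 0.10: √(0.18/27) = 0.082, half-width about 16 points.
- π = 0.10, p = 0.19: √(0.3078/27) = 0.107, half-width about 21 points.
- π = 0.20, p = 0.28: √(0.4032/27) = 0.122, half-width about 24 points.

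Prior pain thus shrinks the difference and widens its interval. The first line also shows that the comparison is imprecise at this sample size even with no prior pain.

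**The case against.** **The schedule itself is not visible.** Figure 3 is the assessment schedule, it is not shown, and its legend includes the NRS. Data collection methods says the NRS is obtained by face-to-face interview, so a preoperative NRS asked at interview need not appear in a list of self-completed questionnaires. This stands as a limit, and the fix is conditional on it. Against it, outcome (iv) spells out the NRS times and none is preoperative. The interviews are also shared with nausea and vomiting, which are assessed only after surgery.

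**No case definition is given.** A reader might infer that prior pain will be counted as chronic post-surgical pain. The article does not say so: it gives no cut-off, item wording or site for (vii), and a condensed article may leave these to the full protocol. If the mailed item asks only about pain from the operation, the problem is smaller. What the text supports is that prior and new pain cannot be separated by the measurements it describes.

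**Randomisation.** A reader might also infer bias between the arms. Allocation is randomised 1:1, so prior pain is balanced in expectation. Chance imbalance is part of the sampling variation that the planned confidence intervals already describe; it is not an additional error. This objection stands in full: the harm is inflated incidence, dilution and noise.

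**Acute pain scores.** The absence of a baseline for the NRS comparisons from 2 h to Day 7 might look like a second defect. It is not: a randomised comparison of postoperative scores is valid without one.

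**Conclusion.** The concern holds within these limits. On the schedule as the text describes it, outcome (vii) has no preoperative pain score, patients with prior pain can enter, and pain that predates surgery cannot be told apart from new post-surgical pain at 3 months. The reported incidence would be too high as a measure of post-surgical pain, and a true group difference would be reduced: to 90% to 80% of its size if 10% to 20% of patients have persisting prior pain. Those prevalences, the 10% rate of new pain, and full persistence and scoring of prior pain are assumptions; the article supplies none of them.

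The documents support neither a claim of systematic bias between arms nor a claim that a stated rule counts prior pain as a case. This is one of nine secondary outcomes. The primary outcome, the mean remifentanil infusion rate, and the sample size built on it are untouched. It is a cheap improvement worth making, because the missing information cannot be recovered at the analysis stage.

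**What to change.** 1. Check the Figure 3 schedule and the full protocol. If a preoperative NRS is already there, add it to the text in Primary and secondary outcomes and in Data collection methods.
2. If it is not, add the NRS item used at 3 months to the day-before-surgery packet, with a question on whether the patient has pain now and where.
3. Define outcome (vii) as pain at 3 months that is new, or increased, relative to the preoperative answer.
4. Optionally, use the preoperative NRS as a covariate in the postoperative NRS comparisons. This is a gain in precision, not the correction of an error.

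The cost is one or two extra questions in a packet that patients already complete, and a minor amendment. Patients already enrolled would lack the item, so the report should state how many have it and how the others are handled for outcome (vii).
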